**Fig. 1 Fig1:**
[figure not shown]
Randomized Trial Flowchart

After membrane rupture, if contractions are continuing at 3 in 10 min (i.e., 9 or more in the preceding 30 min) or more and with progressive cervical change of at least 1 cm every 2 h then labour will continue without further augmentation. These participants will not be randomised unless the frequency of contractions reduce, or if cervical change becomes inadequate (< 1 cm every 2 h). However, if contractions reduce to less than 3 in 10 min (under 9 in 30 min) more than 30 min after ARM, then the next randomisation envelope will be opened by a research assistant, and the woman allocated to receive either continued oral misoprostol or an oxytocin infusion. The woman will also be eligible for randomisation if there is no progressive cervical change over this time, even if contracting well. If there is hyperstimulation (more than 5 contractions in 10 min), then any ongoing stimulation with misoprostol or oxytocin will be stopped until the hyperstimulation resolves.

Women randomised to receive misoprostol will receive an initial dose of oral misoprostol 25mcg. The next dose of oral misoprostol will be omitted if moderate or strong contractions are occurring at 3 in 10 min or more (i.e., 9 or more in the preceding 30 min). If contractions subsequently reduce to less than 3 in 10 min (i.e., less than 9 in 30 min) or become irregular or mild, then a further dose of oral misoprostol 25mcg will be administered, so long as 2 h have passed since the last dose. Oral misoprostol 25mcg may be continued every two hours in the event of inadequate uterine activity. In the event of inadequate progress, clinicians will be advised to give additional misoprostol unless the contractions are very strong and frequent. If there is suspicion of fetal distress due to excessive uterine activity then no additional misoprostol will be administered and terbutaline 250 µg will be given subcutaneously.

Women randomised to oxytocin will receive an oxytocin infusion through an intravenous cannula with an electronic infusion set. Five units of oxytocin will be injected in 500 mL of Ringer’s lactate, started at a rate of 2 mU/min, and increased every 30 min by 2 mU/min until there are three to four contractions every 10 min. The rate will be titrated to maintain that contraction frequency, with a maximum dose of 20 mU/min. If contractions exceed five contractions in 10 min then the oxytocin infusion will stopped and the infusion restarted at half the rate. If there is suspicion of fetal distress due to excessive uterine activity then the oxytocin infusion will be stopped. Terbutaline 250 µg subcutaneously will be given if excessive uterine activity persists.

For women in both groups, research staff will assess temperature and pulse every 2 h and the treating provider will perform a vaginal examination every 4 h to assess cervical dilation and progress. Research staff will document contraction strength and frequency every 30 min and with any change in the infusion rate. Initial fetal monitoring will be with a Fetal Pinnard’s stethoscope or fetal Doppler auscultation every 30 min as per hospital policy. Continuous electronic fetal monitoring will be commenced in the event of abnormalities detected on intermittent auscultation, but discontinued again if the fetal heart rate tracing is normal. Research staff will document the indication for and use of the cardiotocograph. Magnesium sulphate, steroids and anti-hypertensives will be given as per hospital protocols at provider discretion.

Research staff will ask all those recruited (whether eventually randomised or not) to complete an adapted version of the Mother-Generated Index (MGI) survey, the Mother Generated Birth Satisfaction Index (MGBSI) during the study [10, 11]. Research staff will administer a questionnaire at the time of recruitment to record the woman’s priorities and expectations for the induction process and labour. The research staff will administer a second questionnaire 24 h after the birth to assess the woman’s satisfaction with her pre-determined priorities, plus any other important issues. Together, the questionnaires will provide a quantitative satisfaction score as well as qualitative insights into the scoring. Research staff will also conduct a post-study interview with the woman 24 h after delivery and prior to discharge from the study hospital in order to document future preferences for induction of labour methods and overall acceptability of labour induction method.

During their time in the study, research assistants will enter participant’s non-identifiable study data directly into a password protected electronic case report form (REDCap, Vanderbilt University, Tennessee). Data on pregnancy and neonatal outcomes will also be collected from the hospital maternity records. The data will be stored on the handheld device until the device is synchronised through an encrypted link with the host server. Data will be stored on a password-protected secure server located in India. Only researchers from the study will have access to the data.

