### Outcomes

The primary outcome will be caesarean birth, a core outcome used in the Cochrane Collaboration induction of labour generic protocol [12], as the induction of labour core outcome set [13] had not been published at the time of protocol development. A tble of assessments is shown in Table 1. The need for caesarean birth combines the efficacy of the induction (important when induction is being conducted for hypertension in pregnancy) with the safety of the induction process for mother and fetus. It is a particularly important outcome as caesarean birth poses a serious risk to maternal health in the context of the setting and hypertensive disease. Secondary outcomes will include measures of efficacy of the induction process (randomisation to birth interval; vaginal births within 12 and 24 h of randomisation; duration of hospital stay); additional outcomes to allow meta-analysis (start of induction to birth interval; cervix unchanged at 12 and 24 h after the start of cervical preparation; vaginal births within 12 and 24 h after the start of cervical preparation); maternal complications (uterine tachysystole (defined as > 5 contractions in 10 min), uterine hypertonus (defined as a single contraction lasting over 2 min); and hyperstimulation syndrome (tachysystole/hypertonus with associated fetal heart rate abnormalities); uterine rupture; instrumental vaginal delivery; severe hypertension and HELLP Syndrome; maternal vomiting, diarrhoea or fever; antibiotic use; postpartum haemorrhage (> 1,000 ml, or any bleeding leading to systolic blood pressure less than 90 mmHg or diastolic blood pressure less than 60 mmHg or blood transfusion)) and serious maternal complications (intensive care unit admission; septicaemia; pulmonary oedema; cerebral haemorrhage or oedema; renal failure; eclampsia and maternal death). Maternal satisfaction will be assessed using a ‘Mother Generated Birth Satisfaction Index.’ Health economic data will also be collected to allow a full economic analysis of the intervention.

**Table 1 Tab1:** Schedule of enrolment, interventions and assessments

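### An extra contraction record is tied to infusion-rate changes, so a tachysystole episode noticed between rounds must be recorded on oxytocin but, as written, need not be on misoprostol

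*Protocol article*

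**What the plan says.** In the protocol article, Methods, Procedures, monitoring after randomisation is set out in one paragraph that begins "For women in both groups, research staff will assess temperature and pulse every 2 h". The same paragraph gives the contraction-recording rule: "Research staff will document contraction strength and frequency every 30 min and with any change in the infusion rate".

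On oxytocin the rate can change in several ways:
- Routine titration: the rate is "increased every 30 min by 2 mU/min until there are three to four contractions every 10 min".
- Maintenance: "The rate will be titrated to maintain that contraction frequency, with a maximum dose of 20 mU/min".
- Excessive contractions: "If contractions exceed five contractions in 10 min then the oxytocin infusion will stopped and the infusion restarted at half the rate".
- Fetal concern: "If there is suspicion of fetal distress due to excessive uterine activity then the oxytocin infusion will be stopped".

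Misoprostol is given as single oral doses at least 2 h apart, so there is no rate to change. A general rule earlier in Procedures covers both drugs when there is hyperstimulation: "any ongoing stimulation with misoprostol or oxytocin will be stopped until the hyperstimulation resolves". It prescribes an action and attaches no contraction record to it.

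Among the secondary outcomes for the mother, the Outcomes section lists: "uterine tachysystole (defined as > 5 contractions in 10 min), uterine hypertonus (defined as a single contraction lasting over 2 min". It adds a third, hyperstimulation syndrome, which is either of these with fetal heart rate abnormalities. The trial is open-label, and the Statistical analysis section sets p < 0.01 for secondary outcomes.

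**The concern.** The rule is presented as common to both arms, but its second trigger can fire in only one of them. That trigger is also linked to the outcome, because the count that forces the infusion to be stopped and halved is the count that defines tachysystole. On oxytocin, an episode noticed between rounds leads to a rate change and so to a mandatory contraction record. On misoprostol, the same episode between doses often leaves nothing running to stop, and the text asks for no record at that moment. If it settles before the next round, it may not reach the contraction form.

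At stake is the between-arm comparison of tachysystole, and of hyperstimulation syndrome where it arises through tachysystole. Both bear closely on the relative safety of the two drugs. More complete recording on oxytocin would make misoprostol look safer, or could mask a true excess on misoprostol.

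**Working it through.** The article states no figure on this point, so there is none to reproduce. The check has a logical part and an illustration of size.

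**1. Routine titration adds no looks if the clocks are shared.** The start rate is 2 mU/min, the step 2 mU/min, the maximum 20 mU/min and the interval 30 min (all from Procedures). The number of upward steps is (20 − 2)/2 = 9, at 30, 60, ..., 270 min. Rounds are also every 30 min, so on a shared clock all 9 steps coincide with a scheduled record and add none. The asymmetry rests on off-schedule changes, whose number the article does not give.

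**2. What an episode noticed between rounds sets off, by arm.**

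| | Oxytocin | Misoprostol |
|---|---|---|
| Threshold | more than 5 in 10 min | more than 5 in 10 min |
| Action stated | infusion stopped, restarted at half rate | ongoing stimulation stopped; between doses there may be nothing to stop |
| Rate change? | yes | not possible |
| Contraction record required then? | yes | none stated |

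The rate change follows an episode already seen. The difference is therefore in recording what is noticed, not in how often staff look.

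**3. Which outcomes are touched.** The rule covers strength and frequency. Tachysystole is defined by frequency and is directly affected. Hypertonus is defined by the duration of a single contraction, which the rule does not mention. Caesarean birth does not depend on contraction records.

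**4. Illustration of size.** Assumptions, not from the article: equal true rates; a recorded rate on misoprostol of m = 5% or 10%; a relative detection gain g on oxytocin, so that the oxytocin recorded rate is o = m(1 + g). From the article: 260 women per arm and a secondary threshold of 0.01 (critical value 2.576, two-sided).

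- Spurious risk ratio (misoprostol v oxytocin) = 1/(1 + g).
- SE = √[m(1 − m)/260 + o(1 − o)/260].
- Chance of a false finding favouring misoprostol = Φ((o − m)/SE − 2.576).

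Worked case, m = 0.10 and g = 0.5: o = 0.15; SE = √[(0.0900 + 0.1275)/260] = 0.0289; 0.05/0.0289 = 1.73; Φ(1.73 − 2.576) ≈ 0.198.

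| Gain g | Spurious RR | False finding, m = 5% | False finding, m = 10% |
|---|---|---|---|
| 0% | 1.00 | 0.5% | 0.5% |
| 5% | 0.95 | 0.7% | 0.9% |
| 10% | 0.91 | 1.0% | 1.4% |
| 20% | 0.83 | 1.9% | 3.2% |
| 50% | 0.67 | 8.1% | 19.8% |

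The direction is fixed by the wording. The position within this range is not.

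**The case against.** The strongest reply is that a noticed misoprostol episode has other routes into the data. Table 1 collects maternal complications during allocation, at 24 h after birth and from case notes after discharge. Procedures also takes pregnancy outcomes from hospital maternity records, and it requires action on hyperstimulation with either drug and terbutaline on misoprostol where fetal distress from excessive activity is suspected. The article does not say that tachysystole is derived from the contraction form alone. This stands, and it is why the effect may be negligible. It does not restore symmetry, because those routes exist in both arms while the mandatory extra record exists in one.

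A second reply is that Procedures expresses contraction frequency over the preceding 30 min, so a 30-min round may already cover the whole interval. This also has force. It undercuts larger figures that a reader might derive by assuming that each round counts only the last 10 min. On that assumption a 20-min episode is caught with probability (20 − 10)/30 = 0.33. If 25% to 100% of missed episodes then trigger an infusion change, oxytocin detection is 0.50 to 1.00 and the spurious risk ratio 0.67 to 0.33. The article does not support that look-back. The 30-min wording does not fully settle the matter either, because it serves dosing and randomisation decisions. A 30-min total can also hide a burst: 6 + 3 + 3 = 12 in 30 min averages 12/3 = 4 in 10 min.

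A third reply is that form content and derivation rules usually sit in the full protocol or analysis plan, which are not shown. That is fair as to what is absent. The point here is that the recording rule the article does state is uneven between the arms.

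**Conclusion.** The point holds as a one-directional asymmetry in recording, of unknown and possibly negligible size. It affects tachysystole and, through it, hyperstimulation syndrome, both secondary outcomes, in an open-label trial. The risk ratios of 1.00 to 0.67 rest on assumed recorded rates and detection gains, and show only that the effect could run from nothing to material.

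A reader might infer more, and the article does not support it:
- That contractions are looked for more often on oxytocin. Routine steps can coincide with the rounds, and the stop-and-halve step records an episode already noticed.
- That the safety comparison is biased. It is open to bias; whether bias occurs depends on how often rates change off schedule and on how completely the other data sources capture misoprostol episodes.
- That hypertonus is affected in the same way. It is defined by duration, and the rule covers strength and frequency.
- That the primary result is threatened. Caesarean birth is not ascertained through these records.

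**What to change.** Make the extra record symmetric. Replace the infusion-rate trigger with one that either arm can meet: the same contraction record is completed whenever excessive contractions are noticed, or whenever treatment is stopped, withheld, restarted or changed because of contractions.

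Flag each record in the electronic case report form as scheduled or unscheduled. Use all records for the main comparison of tachysystole, and repeat it on the common 30-min records as a sensitivity analysis. The restricted comparison should not be the main one, because it discards genuine episodes that staff saw and acted on.

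The cost is one sentence in Procedures, one flag in the REDCap contraction form, and a little extra form completion in the misoprostol arm. No treatment rule, outcome definition or sample size changes.

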### Outcomes

The primary outcome will be caesarean birth, a core outcome used in the Cochrane Collaboration induction of labour generic protocol [12], as the induction of labour core outcome set [13] had not been published at the time of protocol development. A tble of assessments is shown in Table 1. The need for caesarean birth combines the efficacy of the induction (important when induction is being conducted for hypertension in pregnancy) with the safety of the induction process for mother and fetus. It is a particularly important outcome as caesarean birth poses a serious risk to maternal health in the context of the setting and hypertensive disease. Secondary outcomes will include measures of efficacy of the induction process (randomisation to birth interval; vaginal births within 12 and 24 h of randomisation; duration of hospital stay); additional outcomes to allow meta-analysis (start of induction to birth interval; cervix unchanged at 12 and 24 h after the start of cervical preparation; vaginal births within 12 and 24 h after the start of cervical preparation); maternal complications (uterine tachysystole (defined as > 5 contractions in 10 min), uterine hypertonus (defined as a single contraction lasting over 2 min); and hyperstimulation syndrome (tachysystole/hypertonus with associated fetal heart rate abnormalities); uterine rupture; instrumental vaginal delivery; severe hypertension and HELLP Syndrome; maternal vomiting, diarrhoea or fever; antibiotic use; postpartum haemorrhage (> 1,000 ml, or any bleeding leading to systolic blood pressure less than 90 mmHg or diastolic blood pressure less than 60 mmHg or blood transfusion)) and serious maternal complications (intensive care unit admission; septicaemia; pulmonary oedema; cerebral haemorrhage or oedema; renal failure; eclampsia and maternal death). Maternal satisfaction will be assessed using a ‘Mother Generated Birth Satisfaction Index.’ Health economic data will also be collected to allow a full economic analysis of the intervention.

**Table 1 Tab1:** Schedule of enrolment, interventions and assessments

	**STUDY PERIOD**			
Procedures	Enrolment	Allocation	Post-allocation	
			24 h after birth	Data taken from case notes after discharge
**ENROLLMENT**				
Assessment of eligibility criteria	X	X		
Signed consent form	X			
Randomisation		X		
**INTERVENTIONS**				
Administration of study intervention (misoprostol or oxytocin for augmentation)		X		
**ASSESSMENTS**				
Caesarean Birth		X		
Maternal complications		X	X	X
Fetal / neonatal complications		X	X	X
Serious maternal complications		X	X	X
Cost effectiveness				X
Efficacy of induction process			X	
Assessment of adverse events			X	X
Mother Generated Index	X		X	
Participant Satisfaction Questionnaire			X	

Fetal or neonatal outcomes include neonatal morbidity (meconium-stained liquor; meconium-aspiration syndrome; fetal heart rate abnormality; Apgar score less than seven at five minutes; neonatal intensive care unit admission; seizures; neonatal encephalopathy (as assessed by the Sarnat score)); stillbirth; and perinatal death.

### Sample size calculation

The sample size was estimated based on the primary outcome of caesarean birth assuming a rate of 31% caesarean birth for those receiving oxytocin for augmentation following cervical preparation with oral misoprostol. This is based on published data from a prior trial conducted in this population [14]. A total sample size of 520 women will provide (a) 90% power to detect a reduction in the caesarean rate from 31% to 18.5% (Relative Risk (RR) 0.6), or (b) 80% power to detect a reduction in the caesarean rate from 31 to 20% (RR 0.65) in those women who receive misoprostol (two sided α = 0.05). We estimate that we will need to approach and gain consent from 1,000 women requiring induction of labour for hypertension in order to find 520 who require augmentation after cervical preparation. When augmentation is indicated, consented women will be randomised either to a protocol of continued oral misoprostol (n = 260) or to the standard oxytocin infusion (n = 260).

### Statistical analysis

The trial statistician will provide the Independent Data and Safety Monitoring Committee (IDSMC) with a blinded report every 6 months via email for safety monitoring and will conduct one planned formal interim analysis after 200 women have been recruited. The interim analysis will be for safety and for effectiveness but not for futility; stopping rules will be in accordance with O’Brien-Fleming rules [14] whereby the effective alpha level will be 0.0054 (z = 2.782) for the interim analysis and 0.0492 (z = 1.967) for the final analysis. The IDSMC will have the authority to request further interim analyses if indicated; in the unlikely event this should this occur, revised stopping rules based on the O’Brien-Fleming principles will be calculated according to whether the additional analyses are requested before or after the formal interim analysis at 12 months.

Safety reporting of Serious Adverse Reactions will occur from the period of randomisation until 48 h or discharge, whichever is sooner. Reporting procedures will comply with regulatory authorities in the United Kingdom and India. Trial monitoring will be performed by staff at Gynuity Health Projects on behalf of the sponsor in accordance with the MOLI trial monitoring plan. The research team will share important protocol modifications with relevant parties including investigators, IRBs, trial registries and trial participants as appropriate and in compliance with relevant laws and regulations.

The primary analysis will be performed according to the intention-to-treat principle. The primary outcome measure will be evaluated using binomial regression models, initially unadjusted and then after adjustment for important potential confounding variables and covariates. Binomial regression will be used for binary categorical measures, while ordinal regression will be used for multi-category variables. Count variables will use Poisson regression models and time measures using Cox proportional hazards regression models. All findings will be reported in accordance with the CONSORT guidelines for randomized trials.

All regression models will be run unadjusted (i.e., with treatment group as the only independent/ predictor variable) and then re-run with adjustment for important potential confounder variables/ covariates. These include (but are not necessarily confined to) mother’s age, gestational age, cm dilatation before randomisation, receipt of magnesium sulphate in last 12 h, current anti-hypertensive use, time from hospital admission to randomisation of < 24 h, diastolic blood pressure at enrolment, proteinuria at enrolment, parity, and booked pregnancy. Other potential covariates will include variables found to differ by a clinically significant amount at baseline (post-randomisation) and measures identified as potentially affecting outcome during the study period. Subgroup analysis will be by site of delivery, parity and gestational age. Within the constraints of the O’Brien-Fleming stopping rules, overall statistical significance (across the interim and final analyses) will be set at the conventional 5% level for primary outcomes and p < 0.01 for secondary outcomes. A statistical analysis plan will be completed prior to prior to the first comparative monitoring report to be presented to the IDSMC.

The ISDMC will oversee the safety of participants in the trial. The terms of reference of the ISDMC will be developed separately, based on the principles developed by the DAMOCLES group. The ISDMC, who will have full access to the trial results analysed by allocation, will report directly to the TSC with recommendations about the conduct of the trial as well as whether to continue or stop the trial. The ISDMC will have the following independent voting members: [name] (London School of Hygiene and Tropical Medicine), [name] (Maulana Azad Medical College and Loknayak Hospital, New Delhi), [name] (Burnet Institute, Melbourne), and [name], (The University of Manchester).

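### The stated O'Brien-Fleming limits are shaped for a look at half information (260 of 520), but the interim is placed at 200 women, so stopping early for effectiveness is easier than the named rule allows

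*Protocol article*

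**What the plan says.** Under Statistical analysis, the protocol article sets "one planned formal interim analysis after 200 women have been recruited". It covers safety and effectiveness but not futility. The article says that "stopping rules will be in accordance with O’Brien-Fleming rules", and gives the constants: "the effective alpha level will be 0.0054 (z = 2.782) for the interim analysis and 0.0492 (z = 1.967) for the final analysis".

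The same paragraph lets the monitoring committee ask for further looks, with revised rules that depend on whether they are requested "before or after the formal interim analysis at 12 months". Later in that section, significance for the primary outcome, taken across the interim and final analyses, is promised at 5%.

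Under Sample size calculation the total is 520 women, 260 per arm, with two-sided alpha of 0.05. The caesarean rates assumed are 31% on oxytocin against 18.5% or 20% on misoprostol.

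**The concern.** An O'Brien-Fleming limit depends on how much of the information is in hand at the look: the earlier the look, the stricter the limit. The article fixes three things that cannot all be true together: the method (O'Brien-Fleming), the time of the look (200 of 520) and the constants. The constants belong to a later look than the one planned.

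At stake is the rule by which an open-label trial may stop for effectiveness with under 40% of its women. A limit that is too lenient there makes an early stop more likely, and trials that stop early tend to report an exaggerated effect. Stopping would also leave the rarer maternal and neonatal outcomes with that same fraction of the planned data. The promise of 5% overall is missed too, though by little.

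**Working it through.** **Inputs** (protocol article). Interim after 200 women; limits 2.782 and 1.967; overall two-sided 5% (all from Statistical analysis). Total 520, equal arms, 31% v 20% or 18.5% (Sample size calculation). Information fraction t = 200/520 = 0.385, reading the 200 as randomised women.

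**1. The stated figures.** Two-sided p for z = 2.782 is 0.0054, and for z = 1.967 it is 0.0492. The conversions from z to p are right.

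**2. The look time that the pair implies.** The classical O'Brien-Fleming shape is c/√t at the interim and c at the end. The ratio is 2.782/1.967 = 1.414 = √2, so t = 1/1.414² = 0.500, that is 260 of 520.

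**3. The limits for the planned look.** Overall alpha is 1 − P(|Z1| < c1, |Z2| < c2), with Z1 and Z2 bivariate normal and correlation √t. Setting c1 = c/√t and c2 = c and solving for 0.05 gives:

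| Look | Interim z (p) | Final z (p) |
|---|---|---|
| 200/520 | 3.169 (0.0015) | 1.965 (0.0494) |
| 260/520 | 2.797 (0.0052) | 1.977 (0.0480) |
| Stated | 2.782 (0.0054) | 1.967 (0.0492) |

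Ratio of interim p-values at 200/520: 0.0054/0.00153 = 3.5. No look time from 0.30 to 0.60 reproduces both stated limits as an exact 5% design.

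**4. Overall alpha of the stated pair.** At t = 0.385 it is 0.0520 (10 million simulated trials also gave 0.0520). At t = 0.5 it is 0.0513. In percentage points the excess over 5% is 0.204. Of this, 0.128 is present even at a true half-way look, and the remaining 0.204 − 0.128 = 0.076 comes from looking earlier.

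**5. Chance of stopping for effectiveness at 200.** With 100 per arm, a pooled z-test and exact binomial probabilities:

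| True rates | Limit 2.782 | Limit 3.169 |
|---|---|---|
| 31% v 20% | 15.7% | 7.9% |
| 31% v 18.5% | 23% | 13% |

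When the stated limit stops a trial whose true rates are 31% and 20%, the mean observed difference is about 20 points against a true 11.

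**6. In counts.** Against 31 caesareans in 100 on oxytocin, 14 on misoprostol gives z = 2.88 and 15 gives 2.69, so the stated limit is crossed at 14 (relative risk 14/31 = 0.45). Twelve gives z = 3.27 and 13 gives 3.07, so the classical limit is crossed at 12 (12/31 = 0.39).

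**7. Cost in power.** With 260 per arm and a final alpha of 0.0494, power is 91.2% for 31% v 18.5% and 82.1% for 31% v 20%. At the full 0.05 it is 91.3% and 82.3%.

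**The case against.** The strongest reply is that the error is small. An overall alpha of 5.2% is 5% to the nearest whole percent, and no conclusion about caesarean birth is likely to turn on it. This stands. A reader might infer serious inflation caused by the early look, but the figures do not support that: about 0.13 of the 0.20 points is there even at half-way, and timing adds only about 0.08.

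A second reply is that departing from one boundary shape is not in itself inflated error. Keeping 2.782 at 200 women with a final z of 1.985 (p = 0.0471) would hold 5%. That is true, but it would no longer be the O'Brien-Fleming rule that the article names, and it is not the final limit that the article states. The factor of 3.5 also depends on taking the classical boundary. Under O'Brien-Fleming-type spending at 0.025 per tail it is about 9, so the direction does not depend on the convention.

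Two stronger readings of the trigger are tempting. One takes 200 recruited as 200 consented, because Procedures says "Research staff will ask all those recruited (whether eventually randomised or not"; that would be about 104 randomised, or 20% information. But the abstract uses the same verb for the 520 in the trial, and a comparison of arms needs randomised women, so 200 of 520 is the natural reading. The other takes 12 months as contradicting 200 women. The article gives no accrual rate, so the two may coincide; nor does anything in it suggest that the look time would be chosen to suit the data. Both are wording to tidy.

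Last, an analysis plan and the committee's terms are to follow, and could correct the limits. That does not excuse constants, timing and total that the article itself fixes inconsistently.

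**Conclusion.** The point holds as a modest but definite error. The constants, the timing and the named method do not fit together. At 200 of 520 the stated interim threshold is about 3.5 times the p-value of the classical O'Brien-Fleming boundary, and overall alpha is 0.0520 rather than 0.0500. The consequence that matters is easier early stopping for effectiveness: roughly double the chance if the truth is 31% v 20%, and a crossing at 14 rather than 12 caesareans against 31 in 100.

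This assumes that the 200 are randomised women with mode of birth known, split equally between arms, that information is proportional to their number, and that normal theory describes the joint behaviour of the two looks.

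**What to change.** Use one of these, before any comparative data are seen:

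- Keep the look at 200 and replace the constants with z = 3.169 (p = 0.0015) and z = 1.965 (p = 0.0494).
- Name an O'Brien-Fleming-type alpha-spending function, state its form, and evaluate it at the actual information fraction. At 200/520 the two-sided 0.05 form gives 3.160 and 1.966; 0.025 per tail gives 3.430 and 1.962. The form must be stated because the interim limits differ. This option also covers extra looks that the committee requests.
- Move the look to 260 and use 2.797 and 1.977. Moving it without changing the constants would leave overall alpha at 0.0513.

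In each case, state the trigger once, as a number of randomised women with mode of birth recorded, and reconcile it with the reference to 12 months.

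The cost is wording in the protocol, the analysis plan and the committee's terms of reference. No extra women are needed and final power is essentially unchanged. With the look kept at 200, early stopping becomes somewhat less likely; with the third option, the look comes later.
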